### Study population and allocation

A total of 80 KOA patients will be recruited from the outpatient of the Affiliated Hospital of Southwest Medical University, as well as from some communities in the city by means of advertisements. The inclusion criteria are as follows: those with osteoarthritis in at least one knee according to the American College of Rheumatology Classification Criteria established in 1995 [22]; those aged over 50 years; those with the self-reported average knee pain > 2.0 and < 7.0 measured by the Visual Analogue Scale (VAS) for most days in the month; and those with the Kellgren-Lawrence grade (K-L grade) for KOA of II-IV. KOA will be confirmed through physical examinations and radiography. For participants with bilateral KOA, the more seriously affected side (as identified by K-L grade of KOA and the pain intensity) would be selected as the affected leg.

In the meantime, the exclusion criteria are shown as follows: patients with the age of ≥70 years; those undergoing hip or knee muscle training in the past 4 weeks; those with obvious knee varus or valgus deformity; those who have taken oral corticosteroid within the last 4 weeks or intraarticular corticosteroid injection within the last 3 months; those with systemic arthritic conditions; those who had undergone tibial osteotomy, hip or knee joint replacement, or other surgeries of knee or hip joint; and those with any other neurological, muscular or joint diseases that may affect the lower limb function.

Patients will be recruited in strict accordance with the inclusion and exclusion criteria, and will be subsequently assigned randomly into the Quadriceps-plus-hip-abductor-strengthening group (experiment group) and the Quadriceps-strengthening group (control group) at the ratio of 1:1. Specifically, the randomization sequence will obtained by an independent researcher not taking part in the treatment or assessments using the random number function in Excel. Allocation will be hiden in serial number, with opaque envelopes placing in the central location. In addition, another researcher participating in the study will then open the envelopes in sequence after patient recruitment and baseline assessment.

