### Outcomes

Participants will be assessed by other physiotherapists blinded to the group allocation at different time points based on different assessments shown in Table 1. Additionally, baseline age, gender, symptoms, disease severity (K-L grade), duration, previous treatment and medication will be recorded using a questionnaire (in week 0). The primary outcome is the overall pain assessed using VAS in the 6th week, while the secondary outcomes include the overall function measured by the Western Ontario and McMaster Universities Osteoarthritis Index (WOMAC), as well as the quality of life assessed by MOS Item Short-form Health Survey (SF-36), and several functional tests.

**Table 1 Tab1:** Schedules for follow-up assessments and date collection

Assessments	Baseline	Active strengthening at home						Follow-up	
	Week 0	1st week	2nd week	3rd week	4th week	5th week	6th week	8th week	12th week
VAS for pain	√	√	√	√	√	√	√	√	√
WOMAC	√						√	√	√
SF-36	√						√	√	√
FTSST	√						√	√	√
Step test	√						√	√	√
Stair ascent/descent task	√						√	√	√
Figure-of-8 Walk Test	√						√	√	√
Adverse effects		√	√	√	√	√	√	√	√

The overall pain intensity in the involved knee within the past 1 week will be self-measured by patients using the VAS, with terminal descriptors ranging from 0 (no pain) to 10 (maximal pain). Meanwhile, the overall function of patients will be assessed adopting WOMAC, a disease-specific scale with high reliability and validity [23]. WOMAC is comprised of 24 items assessing pain (scored 0–20), stiffness (scored 0–8) and physical functions (including personal care, walking, sitting, lifting, sleeping, standing, social life and travelling) (scored 0–68). Every item is rated on a scale of 0–5, with a higher score indicating a worse symptom. Moreover, the quality of life will be measured by SF-36 constituted by eight dimensions, including mobility, pain and discomfort, daily activities, depression and anxiety, and self-care [24].

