### Sample size

The sample size is calculated with reference to relevant previous studies. Notably, a change in VAS of knee pain is estimated to be 2.0 between two groups after the strengthening program, which suggests clinically important change. Meanwhile, the standard deviation (SD) between the experiment and the control groups is estimated to be 2.5 based on relevant previous publications [20]. Moreover, the sample size required for each group is about 33 when a two-tailed test with the power of 90% and the significance level of 5% (α error) is applied. Eventually, the total sample size is calculated to be 80 after taking into consideration a 1:1 allocation ratio and a dropout rate of 20%.

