### Statistical analysis

Statistical analyses will be performed following the per-protocol (PP) analysis and intention-to-treat (ITT) analysis. Typically, PP analysis would be conducted if no participants have dropped out of the trial for any reason. In addition, the rule of last-observation-carried-forward will be applied for the missing data when performing ITT analysis. Additionally, baseline data will be analyzed and adjusted using the covariance analysis if no statistically significant differences between two groups and a possibility of covariance of baseline data are found. Categorical data, such as gender or those expressed as frequencies (%) will be analyzed using chi-square test or Fisher’s exact test. Non-parametric statistical tests will be applied for data not conforming to normal distribution. In addition, statistically significant differences in intra-group and intergroup data will be analyzed by repeated measure analysis of variance. All statistical analyses will be performed using the SPSS 19.0 statistical software by a statistician blinded to the allocation. The significance level is set at 5%.

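### The primary week-6 VAS comparison is parametric or rank-based depending on the observed distribution, so neither the test nor the quantity estimated is fixed

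*Protocol article*

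**What the plan says.** Under Outcomes, the protocol article states: "The primary outcome is the overall pain assessed using VAS in the 6th week". The scale runs from 0 to 10. Under Study population and allocation, entry requires "self-reported average knee pain > 2.0 and < 7.0".

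Under Sample size, the trial is planned on a difference in means: "a change in VAS of knee pain is estimated to be 2.0 between two groups", with SD 2.5, 90% power, two-sided 5% and about 33 per group.

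Three sentences under Statistical analysis bear on the primary test:

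- The distribution rule: "Non-parametric statistical tests will be applied for data not conforming to normal distribution".
- The comparison method: "statistically significant differences in intra-group and intergroup data will be analyzed by repeated measure analysis of variance".
- A baseline adjustment that is itself conditional: "baseline data will be analyzed and adjusted using the covariance analysis if no statistically significant differences between two groups".

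No sentence says that the primary outcome escapes the distribution rule. The text also does not say whether normality is judged on raw scores, change scores or model residuals.

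**The concern.** This is a stated decision rule, not an omitted detail. It lets the week-6 data choose between two analyses that answer different questions. A mean comparison estimates VAS points, the unit in which the trial was sized. A rank test such as Mann-Whitney does not, so its result could not be set against the 2.0-point target. Applied to week-6 scores, it also leaves out baseline VAS, which every patient provides.

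The bounded scale makes the switch a practical possibility. Patients enter between 2 and 7, and a gain of about 2 points moves some of them towards 0, where raw scores become skewed. The rule also protects against little: with 32 to 40 per arm, a comparison of means does not need normally distributed raw scores.

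**Working it through.** **The plan's own figure.** For two means, n per group = 2 × (1.960 + 1.282)² × 2.5² / 2.0² = 2 × 10.51 × 1.5625 = 32.8, so 33. This reproduces the protocol. Adding 20% gives 33 × 1.2 = 39.6, so 40 per arm and 80 in total. The calculation is an unadjusted comparison of means.

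**Simulation inputs.** From the protocol: SD 2.5, difference 2.0, bounds 0 and 10, baseline between 2 and 7, 33 per arm. Assumed, because the protocol does not give them: baseline uniform on that range; control week-6 mean 3.0 to 4.5; baseline to week-6 correlation 0.3 to 0.7; Shapiro-Wilk at 5% as the check (in either arm for scores, pooled for residuals); Mann-Whitney as the rank test. Week-6 values are normal, clipped to 0-10. There are 1,200 runs per cell, except the rows for control mean 3.5, which use 32 per arm (3,000 runs for firing rates and the t-test, 4,000 for ANCOVA).

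**What clipping does.** With control mean 3.5 the treated latent mean is 1.5, and the share at 0 is about Φ(−1.5/2.5) = Φ(−0.6) = 27%. With control mean 4.0 it is Φ(−0.8) = 21%. The realised mean difference is then about 1.65 to 1.75 points, not 2.0.

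**How often the switch fires**, correlation 0.5: latent 2.0-point effect, with no effect in brackets.

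| Control mean | Raw week-6 scores | Change scores | ANCOVA residuals |
|---|---|---|---|
| 3.0 | 99.7% (59.6%) | 18.5% (14.6%) | 32.8% (18.0%) |
| 3.5 | 97% (29%) | 17% (12%) | 22% (10%) |
| 4.0 | 88.3% (14.4%) | 12.5% (9.3%) | 13.2% (6.8%) |
| 4.5 | 68.5% (8.8%) | 13.2% (9.2%) | 9.3% (6.2%) |

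For raw scores at means 3.5 and 4.0, other runs with 32 or 33 per arm gave 97.1 to 97.9% and 85.6 to 87.7%. With SD 1.5 and control mean 4.5, the raw-score rate hardly moves (12% with the effect, 9% without).

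**Power at the latent 2.0-point effect, raw scores checked.** Each switch column uses Mann-Whitney if either arm fails the check, otherwise the named fixed test.

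| Correlation | Control mean | Fixed t-test | t-test with switch | Fixed ANCOVA | ANCOVA with switch | Loss against ANCOVA |
|---|---|---|---|---|---|---|
| 0.3 | 3.0 | 85.9% | 86.5% | 88.6% | 86.5% | 2.1 |
| 0.3 | 4.0 | 88.9% | 88.8% | 90.6% | 89.2% | 1.4 |
| 0.5 | 3.0 | 85.2% | 84.8% | 92.9% | 84.8% | 8.1 |
| 0.5 | 3.5 | 86.1% | 85.8% | 93.2% | 86.2% | 7.0 |
| 0.5 | 4.0 | 88.4% | 87.9% | 95.1% | 89.9% | 5.2 |
| 0.5 | 4.5 | 89.2% | 88.8% | 95.2% | 91.5% | 3.7 |
| 0.7 | 3.0 | 85.8% | 84.2% | 98.0% | 84.2% | 13.8 |
| 0.7 | 4.0 | 88.5% | 88.3% | 98.8% | 90.0% | 8.8 |

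The loss against ANCOVA grows with the correlation, while the loss against the t-test does not exceed 1.6 points in any row. What is lost is the baseline covariate, not efficiency from ranking.

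**If residuals are checked instead**, correlation 0.5, the loss against fixed ANCOVA is 92.9 − 90.6 = 2.3 points at control mean 3.0 and 95.1 − 94.2 = 0.9 at 4.0.

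**Type I error.** The switching rule gave 4.7 to 6.7% in all cells at SD 2.5, within simulation error of the fixed tests.

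**The case against.** The strongest reply is that the power loss is measured against an analysis the protocol never fixes. ANCOVA is conditional there, comparisons are assigned to repeated-measures ANOVA, and the sample size is a plain two-mean calculation. Against an unadjusted t-test the switch costs about 1 point or less in most settings. This stands, so the loss has to be described as forgone baseline adjustment.

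A reader might infer that the switch fires mainly when treatment works. The documents do not support that as a general statement. It holds for raw scores at about the design SD, but largely disappears for change scores, which are a fair reading given that the sample size section speaks of a change in VAS. At control mean 3.0 the raw-score check also fires in about 60% of trials with no effect. The share of patients at exactly 0 comes from the clipping model, not from the protocol.

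The sentence is also generic, and nothing says that mean differences will go unreported. Its application to the primary outcome is the natural reading rather than the only one, and the named check and rank test could be left to a fuller document. Even so, the rule is stated without an exemption, and details added elsewhere would not remove it.

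Finally, the statistician is blinded to allocation. That limits deliberate choice of a favourable test, but it does not stop the data from changing what is estimated.

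**Conclusion.** The point holds in a limited form. As written, the primary test and the quantity it estimates depend on the observed distribution, and the rank branch gives no mean difference to compare with the 2.0 points used for sizing. That conclusion needs no simulation.

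The sizes do rest on the stated assumptions. At control means of 3.5 to 4.0, SD 2.5, correlation 0.5 and a latent 2.0-point effect, the switch fires in about 86 to 98% of trials if raw scores are checked and about 13 to 22% if change scores or residuals are. With raw scores checked, the loss against a fixed ANCOVA is about 5 to 8 points at correlation 0.5 for control means of 3.0 to 4.0. It is 1 to 2 points at correlation 0.3 and up to about 14 at 0.7.

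The documents do not support a claim of inflated false positives, or of a general power cost from ranking itself. The matter should be corrected, but it does not threaten the trial's validity.

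**What to change.** State in the Statistical analysis section that the primary analysis is ANCOVA of week-6 VAS on group and baseline VAS, whatever the distribution. The week-6 contrast from a mixed model with baseline VAS is an equivalent choice. Report the adjusted mean difference with 95% CI, using robust or bootstrap standard errors if residuals are skewed. Remove the normality switch for the primary outcome and keep the rank test as a named sensitivity analysis.

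The change takes about one sentence and needs no new data, visits or patients. The only concession is that skewness is handled through the standard errors and the sensitivity analysis rather than by changing the primary test.

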**Methods:**

A total of 80 subjects with symptomatic KOA will be recruited from the communities and hospital outpatient, and will be randomly assigned to the experiment group (Quadriceps-plus-hip-abductor-strengthening) or the control group (Quadriceps-strengthening). Specifically, participants in the experiment group will complete 4 exercises to train the quadriceps and hip abductor twice a day for 6 weeks at home, while those in the control group will only perform 2 exercises to strengthen the quadriceps. Besides, all patients will also receive usual care management, including health education and physical agent therapy when necessary. Knee pain will be measured using the Visual Analogue Scale (VAS) at baseline, in every week during the course of treatment, as well as 8 and 12 weeks after randomization. Furthermore, knee function will be measured using the Western Ontario and McMaster Universities Osteoarthritis Index (WOMAC) scale, and the quality of life will be measured using the MOS Item Short-form Health Survey (SF-36). In this study, several simple tests will be applied to assess the objective function. All the assessments except for VAS will be carried out at baseline, and in the 6th, 8th and 12th weeks respectively.

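### The primary outcome and sample size concern VAS at week 6, but the stated test is a repeated-measures ANOVA with no visits, deciding term or week-6 contrast named

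*Protocol article*

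**What the plan says.** Three parts of the protocol article bear on this.

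- **Outcomes:** "The primary outcome is the overall pain assessed using VAS in the 6th week". Table 1 schedules VAS on nine occasions: baseline, weeks 1 to 6, week 8 and week 12.
- **Sample size:** "a change in VAS of knee pain is estimated to be 2.0 between two groups after the strengthening program", and "the standard deviation (SD) between the experiment and the control groups is estimated to be 2.5". With a two-tailed 5% level and 90% power this gives about 33 per group, raised to 80 in total for 20% dropout. The programme lasts six weeks (Interventions), so the difference being powered is the one at week 6.
- **Statistical analysis:** "statistically significant differences in intra-group and intergroup data will be analyzed by repeated measure analysis of variance". The section does not list the visits that enter, say whether the group or the group-by-time term decides, or name a contrast at week 6. Non-parametric tests are kept for non-normal data. Analysis of covariance also appears: "baseline data will be analyzed and adjusted using the covariance analysis if no statistically significant differences between two groups". That adjustment depends on a baseline comparison and is not tied to VAS at week 6.

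**The concern.** The endpoint and the sample size describe one quantity: the difference between arms in VAS at one visit. A repeated-measures ANOVA over several visits has two standard terms that involve treatment, and neither is that quantity. The group term compares the arms on their average over visits. If baseline is one of those visits, it contributes an expected difference of zero. The group-by-time term asks whether the difference between arms changes at all over time. With nine visits it has 8 degrees of freedom and gives no single estimate.

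The same sentence covers intra-group differences. These do not compare the randomised arms. Both arms receive quadriceps training, so both can be expected to improve.

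At stake is which result counts as primary. With no deciding term fixed, the group term or the interaction could be presented as the primary result once the data are known, and the stated 90% power describes neither.

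**Working it through.** **Inputs from the article.** Difference 2.0, SD 2.5, two-sided 5%, power 90%, total 80, dropout 20%, nine VAS visits.

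**Assumptions, not in the article.** Equal correlation r between any two visits, taken as 0.3, 0.5 and 0.7; SD 2.5 at every visit; several shapes of the treatment difference over time. Evaluable patients: 40 × 0.8 = 32 per arm.

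**1. The plan's own figure.** For two means at one time, n per arm = 2 × SD² × (z₀.₉₇₅ + z₀.₉₀)² / difference² = 2 × 6.25 × 10.507 / 4 = 32.84, so 33. Then 66 × 1.2 = 79.2, so 80. Both stated figures reproduce. The calculation is a plain two-sample comparison at one time and uses no correlation between visits.

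**2. Week-6 comparison, 32 per arm.**
- Unadjusted: standard error 2.5 × √(2/32) = 0.625, power 88%.
- Adjusted for baseline: the residual SD is 2.5 × √(1 − r²) = 2.38 / 2.17 / 1.79, power 91% / 95% / 99%.

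**3. Nine-visit ANOVA, difference rising linearly to 2.0 at week 6 and then held.** The differences by visit are 0, 0.33, 0.67, 1, 1.33, 1.67, 2, 2, 2.
- Group term: the target is 11/9 = 1.22. The variance of a nine-visit mean is 6.25 × (1 + 8r)/9 = 2.36 / 3.47 / 4.58. The standard error of the difference is √(2 × variance/32) = 0.384 / 0.466 / 0.535. Power comes from the noncentral t on 62 df.
- Interaction: noncentrality = (32/2) × Σ(dⱼ − mean)² / [6.25 × (1 − r)]. With the sum of squares 4.667 this is 17.1 / 23.9 / 39.8. Power comes from the noncentral F on 8 and 496 df.

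| Test (32 per arm) | r = 0.3 | r = 0.5 | r = 0.7 |
|---|---|---|---|
| Week 6, unadjusted | 88% | 88% | 88% |
| Week 6, adjusted for baseline | 91% | 95% | 99% |
| Group term, nine visits | 88% | 73% | 61% |
| Group-by-time, nine visits | 85% | 96% | 99.9% |

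**4. Other shapes, same formulas.**
- Linear rise to 2.0 at week 6, fading to 1.5 at week 8 and 0.5 at week 12: the average is 9/9 = 1.0. At r = 0.5 the group term has 56% power and the interaction 88%.
- Full 2.0 from week 1 onward: the average is 16/9 = 1.78. At r = 0.5 the group term has 96% and the interaction 88%.

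**5. Does a significant interaction imply a week-6 effect?** Take an early, transient difference of 0, 1, 1.5, 1.5, 1, 0.5, 0, 0, 0, which is zero at week 6. The sum of squares is 3.389 and the noncentrality 12.4 / 17.4 / 28.9. The interaction is significant in about 69% / 86% / 98% of trials at r = 0.3 / 0.5 / 0.7. It can therefore be positive with no difference at the primary time point.

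**The case against.** The strongest reply is that the analysis sentence is open rather than wrong. It lists no visits, so the nine-visit model is inferred from the assessment schedule. The sample-size section speaks of a change in VAS, and a repeated-measures ANOVA of baseline and week 6 alone would fit that wording. Its group-by-time term has 1 degree of freedom and is exactly the test of change to week 6. With the SD of a change equal to 2.5 × √(2(1 − r)), its power at 32 per arm is about 76% / 88% / 98%. A week-6 contrast can also be drawn from a longer repeated-measures model. This stands. A reader might infer that the stated method cannot yield a week-6 comparison, and the article does not support that. It does not say that this comparison will be made or will decide.

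Three other strong readings also fail:

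- **That the trial loses power.** Only the group term falls well short, and only under some shapes. The interaction often matches or exceeds the unadjusted week-6 test, and the group term does so if the effect appears early.
- **That the ANOVA fails for want of complete data.** The article specifies last observation carried forward for the intention-to-treat analysis. Whether that is a good choice is a separate question.
- **That the conclusion will rest on within-group tests.** Nothing says so. The aim is stated throughout as superiority over quadriceps training alone.

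It can also be said that deciding terms are often left to a fuller plan. That would cover silence. Here the article does name a method, and its standard terms do not match its own endpoint and sample size. The covariance sentence does not close the gap, because it is conditional and not linked to week 6.

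**Conclusion.** The point holds as a mismatch between the named method and the declared quantity. The primary outcome and the 33 per arm concern one between-group difference at week 6. The only between-group test named for normally distributed continuous outcomes is a repeated-measures ANOVA whose visits, deciding term and contrast are not fixed. If all nine VAS visits enter, neither standard term is the week-6 difference, and the 90% power was not calculated for either.

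The size of any power loss cannot be settled from the article. Over r = 0.3 to 0.7, with a linear rise then held and 32 per arm, the group term ranges from 88% down to 61% and the interaction from 85% up to 99.9%. These figures rest on an assumed correlation structure and effect shape and should not be read as the trial's actual power. What does not depend on those assumptions is that the primary test is not identified. A baseline-adjusted week-6 comparison, using data already collected, matches the endpoint and has at least the power of the unadjusted one in every case examined.

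**What to change.** In the Statistical analysis section:

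- Name one primary test: the between-group difference in VAS at week 6, with its 95% confidence interval, at two-sided 5%. Take it from analysis of covariance adjusted for baseline VAS, or from the week-6 contrast of a baseline-adjusted longitudinal model.
- Apply the baseline adjustment unconditionally, not according to a baseline significance test.
- Make the other visits and the overall repeated-measures terms secondary.
- State that within-group changes are descriptive and do not support the superiority conclusion.

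The cost is wording only. No new data are needed because baseline VAS is already scheduled, and the sample size need not rise on this account.
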